### Ethical Considerations

This study has been carried out in accordance with the guidelines of the Hong Kong Metropolitan University Research Ethics Committee (HE-SF2024/34) and was registered in the Chinese Clinical Trial Registry (ChiCTR2400094247).

All potential participants will be provided with a detailed digital informed consent form. This form outlines the purpose of the study, procedures, potential risks and benefits, confidentiality measures, voluntary participation, the right to withdraw at any time without penalty, and contact information for the principal investigator. Participants will be required to click the Yes button below the statement “I have read and understood the above information, and I voluntarily agree to participate in this study” to indicate their consent to participate.

To ensure privacy and confidentiality, all data will be anonymized by assigning a unique reference number, which will be used to link all data collected from the game and surveys, rather than using participants’ names. All data will be securely stored in an encrypted folder, with backups stored on a separate encrypted external hard drive to further protect participant confidentiality. Only the research team will have access to the information.

During the design of this study, care was taken to ensure that participants would not be exposed to any physical harm or discomfort. To prevent potential harm, all participants will be required to undergo prescreening to assess any existing health conditions that might contraindicate physical activity, as advised by their health care providers. Participants with such conditions will be deemed ineligible to participate in the study.

## Results

### Study Timeline

Recruitment was initiated in July 2025, and enrollment is ongoing. As of November 17, 2025, we have recruited 19 participants. Data analysis has not yet started. Final data collection is expected to be completed by August 2026, and the results are expected to be published in March 2027. Figure 5 shows the trial flow diagram.

**Figure 5 figure5:**
[figure not shown]
Trial flow diagram.

### Anticipated Findings

We hypothesize that participants in the gamified pain management intervention will report a substantial reduction in pain intensity and pain interference compared with the control group at both postintervention and 3-month follow-up. Furthermore, the gamified pain management group is expected to exhibit greater improvements in secondary outcomes, including emotional distress, fear-avoidance beliefs, and pain catastrophizing, as well as higher engagement and exercise adherence. In addition, recovery is expected to be associated with sex, age, and socioeconomic status.

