**Methods:**

A 2-arm, single-blind randomized controlled trial will recruit 172 participants through Chinese hospitals and online platforms. Eligible participants will be randomized to 2 groups: a 10-week gamified pain management program for the experimental group and routine online pain management materials for the control group. Primary outcomes, including pain intensity and pain interference, and secondary outcomes, including fear avoidance, emotion, exercise adherence, quality of life, and user satisfaction, will be assessed at baseline, after the intervention (10 weeks), and at a 3-month follow-up. A mixed-design ANOVA and intention-to-treat analysis will be used to evaluate intervention effects.

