#### Primary Outcome

Pain intensity and pain interference are assessed using the Brief Pain Inventory between baseline, T1, and T2, rated from 0 (no pain) to 10 (worst pain). Pain severity is calculated based on pain experienced in the past 24 hours and “current pain.” Pain interference includes the degree to which pain interferes with general activity, mood, walking, work, social relationships, sleep, and enjoyment of life. The Chinese version has good reliability, with Cronbach α=0.89 [51].

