### Statistical Analysis

SPSS (version 25.0; IBM Inc) will be used for all statistical analyses. An intention-to-treat analysis will be used, whereby all participants will be analyzed in the context of the groups to which they had been originally assigned. Descriptive statistics for feasibility will include the following: (1) the percentage of participants recruited from the total number approached; (2) the percentage of participants (among those recruited) who are retained in the study at the end of 3 months in each arm and overall; and (3) engagement metrics, including completion status, duration of the intervention, and rate of accuracy on quizzes.

To detect potential differences in sociodemographic and baseline clinical characteristics, the *χ*^2^ test with continuity correction (or the 2-sided Fisher exact test when appropriate) will be used for categorical variables, and the *t* test will be used for continuous variables. The normality of distributions will be confirmed using the Shapiro-Wilk test before statistical analysis. Repeated measures ANOVA (mixed design: within and between groups) will be used to determine the overall effectiveness of the intervention. Missing values will be addressed using intention-to-treat principles with maximum likelihood estimation, assuming data are missing at random. Statistical significance will be set at *P*<.05.

The interviews will be transcribed verbatim and reviewed. Open and axial coding will be used for data identification and integration, resulting in different meaning categories derived using grounded theory methods. NVivo (QSR International Inc) will be used for the coding process and information handling.

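### Two unranked primary outcomes share one P<.05 threshold and one alpha of .05 in the sample size, so the chance of a false primary result is about 7-10%, not 5%

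*Protocol article*

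**What the plan says.** The Abstract (Methods) lists "Primary outcomes, including pain intensity and pain interference" in the plural. The Primary Outcome section puts both under one heading: "Pain intensity and pain interference are assessed using the Brief Pain Inventory between baseline, T1, and T2". Neither outcome and neither time point is ranked above the other.

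Anticipated Findings hypothesizes a reduction in both outcomes "compared with the control group at both postintervention and 3-month follow-up".

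Statistical Analysis names a mixed-design repeated measures ANOVA that "will be used to determine the overall effectiveness of the intervention", without saying which model term or contrast decides. It then sets a single threshold: "Statistical significance will be set at *P*<.05".

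Sample Size uses an effect size of 0.50, power of 0.90 and one two-tailed alpha of .05, and arrives at 172 participants (86 per arm). Of the four pooled estimates behind the 0.50, two (−0.62 and −0.86) are stated to concern pain intensity. The other two (−0.30 and −0.57) come with no named outcome. No time point is given for the power calculation.

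**The concern.** When two outcomes are both primary and each is judged at .05, a significant result on either one can be reported as a positive primary result. The error rate for the primary claim is then higher than the 5% that the threshold and the sample size both imply. With no rule fixed beforehand, the outcome or time point to stress can also be chosen after the results are seen. The stated 90% power describes a single comparison at .05, and the article does not say which comparison that is.

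**Working it through.** **Inputs from the protocol article.** Two primary outcomes (Abstract; Primary Outcome). Two post-baseline time points. Threshold .05 (Statistical Analysis). Two-tailed alpha .05, d=0.50, power 0.90, 86 per arm, 20% margin for dropout and missing data (Sample Size).

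**Assumed input.** The correlations between outcomes and between time points are not in the document. A range of 0 to 0.9 is shown.

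**Step 1: the plan's own figure.** The normal approximation gives n = 2(1.960 + 1.282)²/0.50² = 84.1, so 85 per arm. The two-sample t-test gives 85.03, so 86 per arm and 172 in total, with power 90.3%. So 172 is the size for one comparison at two-sided .05 before any loss. After 20% loss, 86 × 0.80 = 68.8, that is 68-69 per arm, and power is 82.5-83.0%. Whether the 20% margin is really in the 172 is a separate point; it matters here only because power after correction depends on it.

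**Step 2: one test per outcome.** If independent, 1 − 0.95² = 9.75%. With correlation, 1,000,000 simulated draws of normal test statistics under no effect give the chance that at least one is significant:

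| Outcome correlation (assumed) | One contrast per outcome | One 2-df group-by-time test per outcome |
|---|---|---|
| 0 | 9.75% (exact) | 9.7% |
| 0.5 | 9.1% | 9.1% |
| 0.7 | 8.4% | 8.5% |
| 0.8 | 7.8% | 7.9% |
| 0.9 | 7.1% | 7.1% |

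**Step 3: only if T1 and T2 are each tested at .05 for both outcomes.** If independent, 1 − 0.95⁴ = 18.5%. With a product correlation structure (outcome/time): 16.2% at 0.5/0.5, 13.7% at 0.7/0.7, 12.8% at 0.8/0.7 and 11.6% at 0.9/0.7. With 0.9 for both it falls to 9.9%.

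**Step 4: power when the error is controlled (d=0.50, two-sided).**

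| Alpha | 86 per arm | 69 per arm | 68 per arm |
|---|---|---|---|
| 0.05 | 90.3% | 83.0% | 82.5% |
| 0.025 | 84.4% | 74.8% | 74.1% |

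Keeping 90% power at alpha 0.025 needs 2(2.241 + 1.282)²/0.50² = 99.3, so 100 evaluable per arm, or 100/0.80 = 125 per arm recruited.

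**The case against.** **A separate analysis plan may exist, and an article condenses.** Testing order and adjustment are often left to those documents, so their absence alone would not be a finding. What remains is what the article itself fixes: two outcomes of equal standing, one flat threshold and one alpha in the sample size. Followed as written, those three do not give 5%.

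**The analysis is one model per outcome, not four tests.** This stands. A reader might infer that any one of four results (two outcomes at two times) may be claimed at .05, and quote roughly 13-16% as the error rate. The document does not support that. Statistical Analysis specifies no separate T1 and T2 contrasts, so the supported count is two tests and Step 3 is conditional.

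**The hypothesis joins both outcomes and both times.** As a formal rule that everything must succeed, it would not raise the error above 5%. But it stands under Anticipated Findings as an expectation and sets no rule in either direction. If joint success is intended, the plan must say so, and the power for joint success would be at or below the single-comparison figure.

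**The rates count false results in both directions.** Correct. Counting only false claims of benefit roughly halves them, to about 4-5% for two tests, but the matching single-test rate is then 2.5%.

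**Other stronger readings that do not hold.** A reader might say that the trial was sized on pain intensity alone, but two of the four source estimates name no outcome. A reader might also say that the power contradicts the success criterion, but no success criterion is stated.

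**Conclusion.** The point holds in limited form. With one test per primary outcome at .05, the two-sided familywise error is about 7-10% when neither outcome is affected. The range reflects an assumed outcome correlation of 0.9 to 0, and the rate is above 5% at every value examined. The higher range of about 12-18.5% applies only if T1 and T2 are each tested at .05, and it too rests on assumed correlations. The defect lies in the stated combination of two unranked primary outcomes with a single threshold and a single-comparison sample size. It can still be corrected cleanly: Study Timeline reports 19 participants recruited as of November 17, 2025, and no analysis started.

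**What to change.** Before any outcome data are analysed, adopt one of two rules in the protocol and carry it into the analysis plan.

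1. **Equal standing.** Name one time point and apply Holm across the two outcomes: the smaller P value is tested at 0.025 and, if significant, the other at 0.05. Restate power for each outcome at alpha 0.025: about 84% with 86 per arm, or about 74-75% with 68-69 per arm. The cost is this lower power, or a larger sample (Step 4).
2. **Fixed order.** Name one primary comparison, for example pain intensity (the outcome stated for the first two meta-analyses under Sample Size) at a time point that the sponsor declares. List the remaining outcome and time-point comparisons in order, each at two-sided .05, and stop formal claims at the first non-significant result. The first comparison loses no power. The cost is that later comparisons cannot be formally claimed once an earlier one fails.

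Under either rule, state which ANOVA term or contrast decides each comparison. The secondary outcomes can keep their label, since relabelling them is not needed to control the primary error. The change is one of wording; any registered description of the primary outcomes should be checked against it.

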## Discussion

### Principal Findings

This study has demonstrated how gamification can be applied in health care. Gamification has been explored in various studies targeting different populations with diverse health goals. For example, a study conducted in 2024 on the use of virtual reality exergames in pain management showed positive effects for individuals with chronic lower back pain [60]. Given the insufficient adherence and motivation in chronic pain management, this study goes beyond the existing state of the art by developing a gamified pain management intervention, which reinforces patients’ motivation for self-management through an engaging approach combined with real-time feedback on achievements.

In the gamified pain management intervention, we will collect data through log-in time points, quiz responses, points accumulation, and weekly question-and-answer sessions on the gamified pain management platform. The information obtained is used to personalize physical exercises according to participants’ pain locations, thereby enhancing engagement. In addition, the intervention enhances user engagement and motivation by leveraging key principles of SDT. The escape room narrative and avatar role fulfill the need for relatedness by creating an immersive, purpose-driven experience that connects users to a larger mission. The points system, progress tracking, and tiered challenges address competence by providing clear goals, immediate feedback, and achievable milestones that validate skill development. Flexible pacing, pain-specific exercise choices, and optional hidden rooms support autonomy, allowing users to tailor the intervention to their preferences and capabilities. Together, these game mechanics, reinforced by educational content and physical practices, transform pain management into an intrinsically motivating process, consistent with studies demonstrating a moderate fit between SDT and the promotion of exercise and peer support for patients with chronic pain [61]. Furthermore, in the context of gamification, SDT provides a valuable lens for understanding how gamification elements influence motivation and sustain behavior change [62].

This randomized controlled trial was specifically designed to address key questions in the field of gamification research, particularly regarding the efficacy of gamification in pain management and the optimal design of such interventions. To our knowledge, this is the first randomized controlled trial combining gamified designs with education, exercise, and relaxation techniques aimed at chronic pain reduction. Randomization was implemented to prevent selection bias and control for confounding variables. Furthermore, while most existing studies focus primarily on pain intensity outcomes, this study incorporated psychological, perceptual, and satisfaction-related outcome measures to provide a more comprehensive evaluation of the intervention’s effectiveness.

### Limitations

Several limitations of this study warrant discussion. First, the research was conducted exclusively among adults, which may limit the generalizability of the findings. Future studies should aim to expand the applicability of the results by examining the impact of gamification on other populations, such as children, and across various settings. Second, at the time of designing this study, social interaction features were not incorporated into the gamified intervention. Given that loneliness is a common issue among individuals with chronic pain [63], the absence of a social context may have hindered the potential development of social and emotional skills and reduced opportunities to mitigate social isolation. Future research should explore the role of social interaction within gamification to determine whether it enhances engagement and outcomes.

In addition, although a click function was integrated into the exercise videos to monitor participant adherence, this method has limitations. Peer collaboration could potentially offer more benefits in terms of increasing participant engagement and adherence to the intervention. Future studies might consider incorporating more interactive elements, such as peer interactions, to improve the overall effectiveness of the gamified approach. All outcomes rely on self-reported measures or platform-collected data. As a pragmatic trial, medical diagnoses and pain medication details were not clinically verified, which may introduce reporting bias. Participants were recruited online, potentially favoring technologically adept individuals.

Finally, the distribution inequities of digital health care between rural and urban areas [64] and between younger and older adults in China limit the broader feasibility of this study, especially regarding the acceptability of digital games among older adults. Future studies should consider supporting initiative and confidence while preserving intrinsic capacity among older adults and individuals with digital illiteracy [65,66] by providing on-site training and multiple resources, including video-, paper-, or audio-based materials on technology use. These factors may limit generalizability to populations with lower digital literacy or limited internet access. In addition, due to the inherently visible nature of gamified interventions, participants in the intervention group would inevitably recognize their exposure to the gamified program, which may introduce expectation bias or placebo effects.

### Conclusions

This study aims to determine the impacts of online GPM on adults’ pain functioning and well-being. By leveraging a rigorous single-blind, randomized controlled trial design with standardized digital delivery, we provide a framework for assessing the efficacy of gamification in chronic pain management. Our findings may offer critical evidence on how gamified interventions can enhance engagement, adherence, and clinical outcomes, potentially informing future digital health strategies for chronic pain. Furthermore, the implementation of a fully remote trial demonstrates the feasibility and scalability of virtual interventions while ensuring accessibility for diverse populations. Ultimately, this research may help establish gamification as an effective tool for improving self-management in chronic pain, with implications for both clinical practice and digital therapeutic development.

## Abbreviations

SDT: self-determination theory
SPIRIT: Standard Protocol Items: Recommendations for Interventional Trials
